### Sample size

2.8

According to our institutional pilot data, the mean ± standard deviation (SD) time with EEG burst suppression was 10 ± 5.5 min in elderly patients who received cardiac surgery and propofol anesthesia. We set a noninferiority margin of 2 min based on clinical expert advice. To test the noninferiority of remimazolam with α = 0.025 and power = 80 %, 240 patients are required (n = 120 in each group). We consider a loss to follow-up rate of 8 %, and the target recruitment is set at 260 elderly patients (n = 130 in each group). We calculated the sample size using PASS (version 11.0.7, NCSs, LLC).

### Statistical analysis

2.9

Continuous variables will be shown as mean ± SD or medians with interquartile range (IQR), and categorical variables as numbers (%). The two groups will be compared using the student's *t*-test, Mann-Whitney *U* test, χ^2^ test, or Fisher's exact test. The interventional treatment effects of remimazolam vs. propofol will be analyzed using the appropriate effect size (i.e., odds ratio, mean difference, or median difference) with the 95 % confidence intervals (CI). With a noninferiority margin of 2 min, noninferiority of remimazolam can be concluded if the upper boundary of 95%CI for the difference in EEG burst suppression time <2.0 min. For the two secondary outcomes, multiple comparison correction with the Bonferroni approach will be performed, and a significance level of *P* < 0.025 will be applied. For the exploratory outcomes, no multiple comparison corrections will be done. Subgroup analyses will be performed according to age, ASA classification, anesthesia time, and CPB time.

The primary analysis will be conducted in the modified intention-to-treat patient population (i.e., all patients who undergo randomization, receive planned cardiac surgery, and have available outcome data) and in the per-protocol population (i.e., all patients receiving the allocated treatment according to the protocol). We do not have plans for interim analysis or missing data imputation. The SPSS (version 26.0, SPSS Inc) will be used for statistical analyses.

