### Outcomes

2.6

For this noninferiority trial, the primary outcome is the cumulative time with EEG burst suppression, which is obtained from the SedLine system [26]. In addition, we will present the adjusted time with burst suppression (time spent in EEG burst suppression divided by surgical time).

The secondary outcomes include (1) the POD occurrence within the first 5 days postoperatively and (2) duration of perioperative hypotension (a decrease in mean arterial pressure >30 % of baseline which requires interventions). POD will be assessed using the Confusion Assessment Method (CAM) or CAM-ICU at 8:00 and 20:00 in the first five postoperative days. The assessment is based on 4 features: acute onset of mental state fluctuation, inattention, disorganized thinking, and consciousness alterations [27]. Patients presenting both features 1 and 2 with either feature 3 or 4 will be diagnosed as delirious [28,29].

Exploratory outcomes include time with PSI <25, time with SEF <8, intraoperative awareness, perioperative use of vasopressors and inotropes, postoperative complications (including myocardial infarction, heart block, new-onset of atrial fibrillation, respiratory failure, pneumonia, stroke, coma, acute kidney injury, renal replacement therapy, and surgical site infection), postoperative nausea and vomiting, reoperation, mechanical ventilation, duration of stay in ICU, length of postoperative hospital stay, 30-d readmission, and 30-d mortality.

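### The two secondary outcomes are tested at Bonferroni P < 0.025 but reported with 95% confidence intervals, so the intervals do not correspond to the tests

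*Protocol article*

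**What the plan says.** All of this comes from the protocol article.

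- **Family.** Section 2.6 (Outcomes) names two secondary outcomes: "The secondary outcomes include (1) the POD occurrence within the first 5 days postoperatively and (2) duration of perioperative hypotension".
- **Test level.** Section 2.9 (Statistical analysis): "For the two secondary outcomes, multiple comparison correction with the Bonferroni approach will be performed". The threshold for each of the two tests is P < 0.025.
- **Interval level.** The same paragraph gives one general rule for effect measures: "odds ratio, mean difference, or median difference) with the 95 % confidence intervals (CI"). It makes no exception for the secondary outcomes and does not label their intervals as unadjusted or descriptive. The odds ratio is on the list, and it is the natural measure for binary POD, so the rule is not confined to the primary outcome.
- **Tests.** "The two groups will be compared using the student's *t*-test, Mann-Whitney *U* test, χ^2^ test, or Fisher's exact test".
- **Other outcomes.** Exploratory outcomes are uncorrected: "For the exploratory outcomes, no multiple comparison corrections will be done". The primary outcome is sized at α = 0.025 in section 2.8 and judged in 2.9 by the upper limit of a 95% interval.

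**The concern.** A two-sided 95% interval pairs with a test at 0.05, and a test at 0.025 pairs with a 97.5% interval. Elsewhere the plan keeps test and interval in step. For the primary outcome, a one-sided α of 0.025 matches the upper limit of a two-sided 95% interval. For the exploratory outcomes, uncorrected tests suit 95% intervals. Only the two corrected outcomes are out of step.

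POD is the clinical motive for the trial, and many readers take an odds ratio interval that excludes 1 as evidence of an effect. The paper could print such an interval next to a statement that POD did not differ significantly. Recruitment is described as ongoing, so the level can still be fixed before results are known. Choosing it afterwards would look selective.

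**Working it through.** **Inputs.** Two secondary outcomes, P < 0.025 each and 95% intervals (2.6 and 2.9); 120 analysed per group (2.8). Assumed: two-sided tests, since sidedness is not stated and this reading fits Bonferroni; the POD rates used below, which lie within the 10% to 50% incidence quoted in the Introduction.

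**1. The plan's own figure.** 0.05 / 2 = 0.025. It reproduces, and the familywise error of the two tests is at most 0.025 + 0.025 = 5%.

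**2. Width.** z(0.975) = 1.960 and z(0.9875) = 2.241. The ratio is 2.241 / 1.960 = 1.14.

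**3. Joint coverage, if independent.**

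| Intervals | Calculation | Joint coverage |
|---|---|---|
| Two at 95% | 0.95² | 90.25% |
| Two at 97.5% | 0.975² | 95.06% |

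**4. How often test and interval part.** They part when |z| lies between 1.960 and 2.241. With no effect the chance is 0.05 − 0.025 = 2.5% per outcome. With a true effect of 2.1 standard errors it is 55.6% − 44.4% = 11.2%.

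**5. Illustration (assumed counts).** POD in 17 of 120 (remimazolam) against 30 of 120 (propofol):
- Odds ratio = (17/103) / (30/90) = 0.495, log −0.703.
- Standard error = √(1/17 + 1/103 + 1/30 + 1/90) = 0.336.
- 95% Wald interval: exp(−0.703 ± 1.960 × 0.336) = 0.256 to 0.957, which excludes 1.
- Uncorrected chi-square P = 0.034, which fails 0.025.
- 97.5% Wald interval: exp(−0.703 ± 2.241 × 0.336) = 0.233 to 1.052, which includes 1.

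**6. Does changing the level alone suffice?** Not quite, near the boundary. With 16 against 30 events, Fisher P = 0.032 fails, yet the 97.5% Wald interval (0.215 to 0.992) excludes 1. With 17 against 31, uncorrected chi-square P = 0.024 passes, yet the interval (0.224 to 1.003) includes 1. The interval method must match the test as well.

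**7. What Holm would add.** Assume POD of 30% against 15%, 120 per group. The standard error is √(0.30 × 0.70/120 + 0.15 × 0.85/120) = 0.0530, so the effect is 0.15 / 0.0530 = 2.828 standard errors. Power is Φ(2.828 − 2.241) = 72.1% at 0.025 and Φ(2.828 − 1.960) = 80.7% at 0.05. If the outcomes are independent, Holm power for POD is 72.1% + 8.6% × (power for hypotension duration at 0.025):

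| Power for hypotension duration | Holm power for POD |
|---|---|
| 20% | 73.9% |
| 50% | 76.4% |
| 80% | 79.0% |
| 100% (ceiling) | 80.7% |

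**8. Intervals under Holm.** Suppose the second interval were switched to 95% after the first rejection. When the first rejection is near certain, joint coverage is 0.975 × 0.95 = 92.6%. Simulation with independent normal statistics (2 million draws) gave 92.6% for true effects of 5 and 0 standard errors, 93.3% for both at 2.8, and 95.0% only when both were null.

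**The case against.** The strongest reply is that the plan never promises adjusted intervals. It attaches Bonferroni to the significance level, and success on the secondary outcomes is defined by P alone. That rule is clear and valid. **This stands**, and it limits the point. A reader might infer that the secondary tests are uncontrolled, or that the plan breaks a promise of multiplicity protection for its intervals. The document supports neither reading. A 95% interval that excludes no effect beside a non-significant result at 0.025 is a description at two levels. It is not two rival decisions.

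A second reply is that a condensed article leaves interval labelling to the full plan. **This does not stand**: the article states both levels in one paragraph, and they do not match.

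A third reply is that Bonferroni is a legitimate choice. **This stands.** A reader might infer that choosing it over Holm is an error, or that Holm would lift POD power to 81%. Bonferroni is valid. The 81% is a ceiling, reached only if hypotension duration is certain to be significant at 0.025, and the document gives no input for that power.

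**Conclusion.** The mismatch is real and confined to reporting. The two secondary outcomes are tested at 0.025 and given intervals that pair with 0.05. For P between 0.025 and 0.05 the interval will generally exclude no effect while the outcome is declared not significant. The chance is 2.5% per outcome under no effect and about 11% for a true effect near 2.1 standard errors. Joint coverage of the two intervals is about 90%, where about 95% would match the tests.

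This rests on two-sided testing, and the coverage figures also on independence of the two outcomes. The delirium counts and rates are illustrations and the conclusion does not depend on them. The familywise error of the tests, the primary noninferiority analysis and the sample size are unaffected.

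**What to change.** **Change.** Add a sentence to section 2.9: POD and hypotension duration are reported with 97.5% confidence intervals from a method that matches the test used, for example a score interval with the chi-square test or an exact interval with Fisher's test. Keep 95% intervals for the primary and exploratory outcomes, and state that the secondary tests are two-sided.

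**Optional.** Use Holm for the two tests. It is never less powerful than Bonferroni at the same familywise error. Keep both intervals at 97.5% and do not switch the second to 95% after a rejection. The second outcome may then be significant at 0.05 while its 97.5% interval includes no effect, and the report should say so.

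**Cost.** One sentence of wording and two intervals about 14% wider. No extra patients or data.

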### Study design

2.1

This randomized controlled noninferiority trial is conducted at the First Affiliated Hospital of Soochow University. A total of 260 elderly patients who are scheduled for cardiac surgery will be recruited. After the Medical Ethics Committee approved this trial (No. 2021–303), we completed the registration at the Chinese Clinical Trial Registry (identiﬁer: ChiCTR2200056353). We plan to recruit all patients by the end of December 2024. Written informed consent will be obtained. We report this trial protocol in accordance to the Standard Protocol Items: Recommendations for Interventional Trials (SPIRIT) guideline [24]. Table 1 presents the scheduled process of enrollment, interventions, and measurements. Fig. 1 shows the flowchart of patients in this trial.

**Table 1 tbl1:** Schedule of patient enrollment, study interventions, and measurements complying with the SPIRIT statement.

Timepoint	Study Period					
	Enrollment	Allocation	Post-allocation			Close-out
	*Pre-anesthesia visit*	Before surgery	During surgery	postoperative day 1 to 5	Hospital discharge	Postoperative day 30

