### Eligibility criteria

2.2

The inclusion criteria are (1) aged equal to or greater than 60 years, (2) American Society of Anesthesiologists (ASA) classification I to IV, (3) planned to have elective cardiac surgery, and (4) with planned ICU admission. The cardiac procedures include coronary artery bypass grafting and/or valve surgery under cardiopulmonary bypass (CPB).

Exclusion criteria are (1) allergy to study medications, (2) surgical procedures involving aortic arch, (3) use of deep hypothermic circulatory arrest or low flow; (4) preoperative left ventricular ejection fraction <30 %, (5) severe hepatic dysfunction (Child-Pugh class C) or renal replacement therapy, (6) severe chronic respiratory disease, (7) history of mental diseases or taking antipsychotic medications, (8) Mini-Mental State Examination (MMSE) score ≤23, or (9) declined to provide informed consent.

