### Randomization and blinding

2.3

A research assistant not involved in the other parts of the trial generates the random sequence with the use of online randomization (https://www.91trial.com; 1:1, permuted blocks of size 2 or 4). Allocation concealment will be protected by password. According to the randomization results, another research stuff assigns patients into one of the two study groups (the remimazolam group and the propofol group). As remimazolam and propofol have different appearances, the perioperative care team will not be blinded to the study groups; however, they are unaware of the study hypothesis. All patients, data collectors, outcome assessors, and a statistician will be masked to the assignment.

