### Anesthesia

2.4

Patients will receive an ASA routine monitoring. Hemodynamic status will be monitored using the FloTrac/Vigileo (Edwards Lifesciences, CA) via radial artery cannulation. Multimodal brain monitoring with the SedLine® (Masimo, CA) system will be applied to monitor intraoperative EEG continuously. Attending anesthesiologists will receive full education of the characteristic EEG patterns in the SedLine system during propofol and remimazolam anesthesia.

To induce general anesthesia, patients will be administered with intravenous sufentanil 0.5 μg/kg and one of the study medications (remimazolam or propofol, with details described below). Rocuronium 0.8 mg/kg will be given for endotracheal intubation. To maintain anesthesia, patients will receive an infusion of remimazolam or propofol, titrated to an appropriate depth of anesthesia. Intermittent sufentanil 0.1 μg/kg will be given to achieve intraoperative analgesia, and rocuronium 0.1 mg/kg will be administered for neuromuscular block. Patients will receive intraoperative mechanical ventilation (tidal volume 6–8 ml/kg, 12–18 breaths per minute, 50–80 % of oxygen in air) and a standardized normothermic CPB (a continuous nonpulsatile perfusion of 2–2.4 l/min/m^2^). Patients will receive erythrocyte transfusion when hematocrit is ≤ 21 % on CPB and ≤24 % off CPB. Vasoactive and inotropic drugs (phenylephrine, epinephrine, norepinephrine, nitroglycerine, or dobutamine) will be used at the discretion of attending anesthesiologists. To provide prophylaxis of nausea and vomiting, intravenous dexamethasone 5 mg and palonosetron 0.075 mg will be given. Upon the completion of surgery, patients will be admitted to a designated cardiac ICU and receive sedation with a continuous infusion of the study medications until extubation.

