### Data management

2.7

We will collect the demographic data (age, gender, body mass index, smoking status, and education years), baseline data (ASA physical status, comorbidities, preoperative medications, and MMSE score), and perioperative data (surgical type, dose of anesthetics and analgesics, anesthesia time, surgical time, duration of CPB, transfusions). EEG information (left and right SEF, PSI, and burst suppression) will be recorded in SedLine and then data will be analyzed offline. Trained investigators will assess the occurrence of POD using the CAM-ICU or CAM postoperatively. All data will be de-identified and then registered on the web-based database (https://www.91trial.com). A data monitoring committee independent of the study team will conduct an ongoing review of study implementation.

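### Two of the four subgroup factors, anesthesia time and CPB time, are known only after randomization and study drug exposure, so treatment comparisons within them lose the protection of randomization

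*Protocol article*

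**What the plan says.** Section 2.9 (Statistical analysis) lists four subgroup factors in one sentence, all on the same footing: "Subgroup analyses will be performed according to age, ASA classification, anesthesia time, and CPB time".

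Section 2.7 (Data management) sorts these factors by when they become known:
- Age is among the "demographic data (age, gender, body mass index, smoking status, and education years").
- ASA status is among the "baseline data (ASA physical status, comorbidities, preoperative medications, and MMSE score").
- The two durations are among the "perioperative data (surgical type, dose of anesthetics and analgesics, anesthesia time, surgical time, duration of CPB, transfusions").

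In Table 1 (section 2.1) randomization and allocation fall in the column headed "Before surgery". Section 2.4 has the study drug running through the operation: "To maintain anesthesia, patients will receive an infusion of remimazolam or propofol, titrated to an appropriate depth of anesthesia". Section 2.3 says that "the perioperative care team will not be blinded to the study groups".

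Nothing in the article says that planned or predicted durations are meant, or that these two analyses are descriptive.

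**The concern.** Randomization makes the arms comparable within groups defined before allocation. It gives no such assurance within groups defined by something that happens afterwards and that the treatment may alter. If one drug lengthens anesthesia, a patient who would fall in the short half on one drug falls in the long half on the other. The two arms within each half then contain different kinds of patient.

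Two features make this more than a formality.
- **From allocation to duration.** The team managing induction, hemodynamics and weaning knows the drug. Section 2.4 leaves vasoactive and inotropic drugs to the anesthesiologist's discretion, and the Introduction expects the drugs to differ in cardiac depression.
- **From duration to outcome.** The primary outcome is a cumulative time, so more minutes under anesthesia give more opportunity for suppression. The authors allow for a dependence of this kind in section 2.6, where they also report suppression time divided by surgical time.

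At stake is the reading of two planned subgroup displays. They could show a within-subgroup difference that no drug effect on suppression produced. Nor could they guide the choice of drug, since neither duration is known when the anesthetic is chosen.

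**Working it through.** **1. The plan's own figure.** Inputs from section 2.8: SD 5.5 min, margin 2 min, one-sided α 0.025, power 80%, true difference 0. The normal formula n = 2·(1.960 + 0.842)²·5.5²/2² gives 119 per arm. The noncentral t gives 120 per arm (power 0.801; 0.798 at 119). The stated 240 is reproduced, and 240 × 1.08 is about the stated 260. The subgroup factors do not enter this calculation.

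**2. Timing of each factor.**

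| Factor | Class in section 2.7 | Fixed before allocation? |
|---|---|---|
| Age | demographic | yes |
| ASA class | baseline | yes |
| Anesthesia time | perioperative | no |
| CPB time | perioperative | no |

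**3. Size of a possible bias, anesthesia time only.** The article gives only the outcome mean (10 min) and SD (5.5 min). Everything else here is assumed:
- Anesthesia time = 300 + 40U + 40e + shift × arm, where U is unmeasured severity and U and e are independent standard normals. Its SD within an arm is √(40² + 40²) = 56.6 min.
- Suppression time = 10 + bU + noise, total SD 5.5 min, no drug effect, b = 2 or 3.
- Correlation between the two: r = (b/5.5) × (40/56.6), which is 0.26 for b = 2 and 0.39 for b = 3.
- Split at the overall median.

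The mean of a standard normal below a cut c is −φ(c)/Φ(c), whose slope at c = 0 has size (0.399/0.5)² = 2/π = 0.637. The cut lies half a shift above one arm's mean and half a shift below the other's, so within a half

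difference ≈ −0.637 × r × 5.5 × (shift/56.6) = −0.637 × (b/80) × shift.

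| Shift (min) | b = 2 | b = 3 |
|---|---|---|
| 0 | 0 | 0 |
| 5 | −0.08 | −0.12 |
| 10 | −0.16 | −0.24 |
| 20 | −0.32 | −0.48 |
| 30 | −0.48 | −0.72 |

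The negative sign favors the drug that lengthens anesthesia. Simulation of 2,000,000 patients agrees to within about 0.01 to 0.02 min. The offset is the same in both halves, and the overall difference is 0.

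**4. Other assumptions.** A simulation with SD 60 min and r = 0.3 to 0.5 gives about −0.16 to −0.30 min at a 10-min shift, −0.52 to −0.87 min at 30 min, and about 0 with no shift.

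**5. Precision of a half-sample comparison.** With 120 evaluable per arm, a median split leaves about 60 per arm in each half. SE = 5.5 × √(2/60) = 1.00 min, so the 95% CI half-width is about 1.96 × 1.00 = 1.97 min.

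CPB time was not modeled.

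**The case against.** The strongest reply accepts the principle and disputes the consequence.

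- **The shift is assumed.** No section reports a drug effect on duration. Patients go to the ICU still sedated on study drug until extubation (sections 2.4 and 2.5), so recovery, where two hypnotics would most obviously differ in time, appears to fall outside operative anesthesia time. A shift of 5 to 10 min gives only about 0.1 to 0.25 min. This stands, and it is why the range starts at 5 min.
- **CPB time is largely surgical.** An effect of the hypnotic on it is less plausible. This stands; for CPB time the point rests on timing alone.
- **The offset is small against sampling error.** Even 0.7 min is below the SE of 1.00 min for a half-sample comparison. This stands, though a larger sample would not remove the bias.
- **The article is condensed.** Cut-points, interaction tests and labelling can sit in an analysis plan. This stands for those details and they are not criticized. It does not answer the point, because the article names the factors, and a completed duration cannot become a pre-randomization variable in a later document.

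A reader might infer that these splits would create a false subgroup effect, that is, a difference between short and long cases. The calculation does not support that: the offset is equal in both halves, so no false heterogeneity arises under this model. For the same reason an interaction test would not reveal the bias. A reader might also set the offset against the 2-min margin and doubt the noninferiority conclusion. Section 2.9 ties that conclusion to the overall difference, which these splits do not touch.

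**Conclusion.** The point holds as a loss of protection, not as proof of material bias. Section 2.9 gives anesthesia time and CPB time the same standing as age and ASA class, although the article's own data classes and Table 1 place both after allocation and drug exposure.

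If allocation does not affect duration, the bias is 0. If it shifts anesthesia time by 5 to 30 min, and anesthesia time correlates with suppression at about 0.26 to 0.39, the spurious within-subgroup difference is about 0.1 to 0.7 min, equal in both halves. Shifts, SD of anesthesia time and correlations are assumptions; the documents supply none of them. The figures do not extend to CPB time.

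Only these two subgroup analyses are affected. The primary noninferiority test and the sample size of 240 evaluable patients (260 recruited) are not.

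**What to change.** Either of two changes to section 2.9 suffices:
1. Replace anesthesia time and CPB time with procedure type as planned before randomization: CABG, valve or combined.
2. Keep the duration splits only as descriptive displays, labelled non-randomized, with no treatment-effect claims.

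The categories for the first option already stand in the eligibility criteria: "The cardiac procedures include coronary artery bypass grafting and/or valve surgery under cardiopulmonary bypass (CPB"), and those criteria require a planned elective operation. One clarification is needed. Section 2.7 lists surgical type among the perioperative data, which may mean the operation performed. The plan should say that the planned procedure is used and that it is recorded before allocation.

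The cost is a change of wording and, if the planned procedure is not already recorded before allocation, one data field. No patients are added and the primary analysis stays as it is. The downside is that two planned subgroup analyses become descriptive or are dropped, and that a patient whose operation changes in theatre is classified by the planned rather than the performed procedure.
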